## Abstract

**Background:**

Young men who have sex with men (YMSM) and transgender people in the Detroit Metro Area are the only risk group for whom the incidence of HIV and sexually transmitted infections (STI) has increased since 2000, with HIV incidence nearly doubling among youth. Substance use (including alcohol), which is relatively frequent among YMSM and transgender people, creates barriers to the optimal delivery of HIV prevention and care services. Standard HIV counseling, testing, and referral (CTR) is limited in providing strategies to identify and address substance use. Hence, in its current form, CTR may not be serving the prevention needs of substance-using YMSM and transgender people. Brief counseling interventions, grounded in principles of motivational interviewing, may offer a mechanism to meet the HIV prevention and care needs of substance-using YMSM and transgender people.

**Objective:**

This prospective, 4-arm, factorial randomized controlled trial aims to examine the efficacy of an motivational interviewing–based substance use brief intervention (SUBI) on participants’ substance use and engagement in HIV prevention.

**Methods:**

The research implements a prospective randomized controlled trial (Project Swerve) of 600 YMSM and transgender people recruited both online and in person. Eligibility criteria include participants who (1) are between the ages of 15 to 29 years, (2) live in the Detroit Metro Area, (3) self-identify as a man or transgender man or woman, (4) have had sexual contact with a man in the 6 months before enrollment, (5) self-report binge drinking or any substance use in the 3 months before enrollment, and (6) self-report an unknown or negative HIV status upon enrollment. Participants are randomized to receive, 3-months apart starting at baseline, 2 individual sessions. Sessions are CTR-only, SUBI-only, CTR followed by SUBI, or SUBI followed by CTR.

**Results:**

Project Swerve was launched in April 2017 and enrollment is ongoing.

**Conclusions:**

Incorporating a SUBI that utilizes the principles of motivational interviewing into HIV CTR provides an opportunity to tailor counseling services for YMSM and transgender people to address additional client barriers to HIV and STI testing.

**Trial Registration:**

ClinicalTrials.gov NCT02945436; http://clinicaltrials.gov/ct2/show/NCT02945436 (Archived by WebCite at http://www.webcitation.org/6yFyOK57w)

## Introduction

### Background

Young men who have sex with men (YMSM) and transgender people (TG; herein collectively referred to as YMSMTG) are at heightened risk for HIV and other sexually transmitted infections (STI) [1,2]. The 3 major cities in the Detroit Metro Area (DMA)—Detroit, Flint, and Ann Arbor—are represented in the top 5 Michigan counties with greatest increases of new HIV, chlamydia, gonorrhea, and syphilis infections [1]. Consistent with the national epidemic, YMSMTG in the DMA are the only risk groups for whom HIV and STI incidence has increased since 2000, with HIV incidence among YMSM between the ages of 13 and 25 years nearly doubling [1,2]. YMSM accounted for 72% of new HIV infections and over 80% of new syphilis diagnoses among people aged 13-24 years. Over 75% of gonorrhea-HIV coinfections were among YMSM [1,3].

The Centers for Disease Control and Prevention (CDC) have recommended that HIV and STI testing be repeated frequently (3-6 month intervals) for high-risk YMSMTG (ie, having multiple or anonymous partners with whom they have condomless anal intercourse [CAI] and who report engaging in illicit drug use) [2]. Recent recommendations from a CDC working group on HIV testing for men who have sex with men (MSM) suggest that clinicians can consider the benefits of offering more frequent screening (eg, once every 3 or 6 months) to individual MSM at increased risk for acquiring HIV infection, weighing their patients’ individual risk factors, local HIV epidemiology, and local testing policies [2]. Consistent with national trends, YMSM living in the DMA report low adherence to these testing guidelines; data are scant on whether TG in this context are adhering to testing guidelines. In 3 prior studies conducted between 2011 and 2014 with YMSM in this community [4-6], a large proportion of YMSM (15%-36%) had never tested for HIV. Among those who did test for HIV, over 65% reported that they had not tested in the past 12 months. YMSM living with HIV also account for the largest drop-off across the HIV/AIDS continuum of care in the DMA, particularly if they are racial or ethnic minorities and live in neighborhoods characterized by socioeconomic disadvantage [1].

Changes in the use of alcohol, tobacco, and other drugs (ATOD) during adolescence and young adulthood are developmentally noteworthy because they can have short- and long-term consequences that affect one’s adult life trajectory including HIV/STI acquisition [7], development of substance use disorders (SUDs), and disruptions in school and job performance [8-14]. Alcohol and marijuana are the most common substances used by youth. National Survey on Drug Use and Health [15] data for the DMA demonstrated that 12.1% of 18- to 25-year-olds needed, but did not receive, treatment for alcohol use and 6.8% of 18- to 25-year-olds needed, but did not receive, treatment for drug use. Given the known synergy between AOD use and HIV risk among YMSMTG [16-21], there is a need to develop HIV prevention interventions that also recognize and tackle issues of substance use [22].

AIDS Service Organizations (ASOs) often serve and are sensitive to the HIV-related needs of underserved YMSMTG. Delivery of HIV services through ASOs has been an efficient rollout mechanism because they reach and affect large numbers of people efficiently; create and establish grassroots policies and procedures that maximize the adoption and diffusion of interventions while considering the community’s social context; increase program sustainability and advocacy; and incorporate the needs of specific communities into tailored services. At present, however, HIV test counselors situated in ASOs are not trained to comprehensively and systematically screen for and address ATOD use in counseling, testing, and referral (CTR) sessions—the routine procedure used to test for HIV. Preliminary data from our community partners indicate that lack of AOD screening and counseling within CTR is a missed opportunity. The authors of this study [23] and others [7,24,25] have also documented that HIV-positive persons with problematic patterns of alcohol and stimulant use experience difficulties with HIV disease management and display elevated HIV viral load, demonstrating a need for reducing substance use early to avoid complicating disease management.

Consistent with the National HIV/AIDS Strategy’s call [26] to reduce new HIV infections by intensifying prevention efforts in highly impacted communities and increasing rates of routine HIV testing, this protocol outlines an intervention that targets high-risk YMSMTG by including a substance use brief intervention (SUBI) as part of CTR. The intervention builds on prior SUBI research [27-34] and also meets the recommendations of the CDC working group on HIV testing among MSM that recommended more frequent testing among high-risk groups: substance using YMSMTG are clearly at an elevated risk of HIV acquisition and currently underutilize HIV prevention services. Using a consensus approach to conceptualize health behavior change, the model guiding our intervention [35-38] synthesizes social cognitive theories [39], along with the trans-theoretical model of change [40,41] and self-determination theory [42,43]. These theories emphasize social cognitive factors that impact behavior change and have informed ATOD and HIV interventions [12,44-46]. Motivational interviewing (MI) [36], the primary approach used to deliver SUBI, is consistent with these theories [47], focusing on resolving ambivalence about problem behaviors, increasing self-efficacy for change, and enhancing motivation moving toward action [48]. This protocol describes the methods for the testing of the intervention below.

### Objective

The prospective, 4-arm factorial randomized controlled trial (RCT) aims to examine the efficacy of Project Swerve, an MI-based SUBI (intervention) compared with the current standard of care CTR (control) on participants’ substance use and engagement in HIV prevention.

## Methods

### Trial Registration, Ethics, Consent, and Institutional Board Approval

The research and ethics presented in this study has been reviewed and approved by the University of Michigan Institutional Review Board (HUM00105125), in addition to the Data Safety Monitoring Board. The study is also registered on ClinicalTrials.gov (NCT02945436).

### Trial Design

The research activities involve a 4-arm factorial RCT of approximately 600 AOD-using YMSMTG aged 15-29 years in the DMA. We will follow participants for 18 months, with follow-up assessments collected every 3 months.

The intervention comprises 2 visits separated by 3 months. Participants are randomized to receive either CTR (control) or a SUBI-adapted version of CTR (referred to as SUBI; intervention) in each visit. To examine how the sequencing and dosing of interventions impacts efficacy, we randomize at baseline into a factorial RCT. The control arm will receive CTR-only at both study visits 1 and 2. Experimental arm 1 (CTR+SUBI) will receive CTR at visit 1 and SUBI at visit 2. Experimental arm 2 (SUBI+CTR) will receive SUBI at visit 1 and CTR at visit 2. Experimental arm 3 (SUBI+SUBI) will receive the intervention condition at visits 1 and 2. Individuals who test HIV-positive at study visits 1 or 2 will receive case management and linkage to care, as offered routinely by each ASO where study activities take place.

This 4-arm factorial randomized design will help answer 3 important questions: (1) what is the impact of adapting current CTR to include SUBI on HIV engagement in care and sexual- and substance-related risk-taking behaviors among high-risk YMSMTG; (2) what combination of services (CTR-only, CTR+SUBI, SUBI+CTR, SUBI+SUBI) has the greatest impact on engagement in HIV prevention (where engagement in care is defined as routine HIV testing for seronegative YMSMTG and linkage and retention in care for seropositive YMSMTG); and (3) if effective, what are the costs of delivering SUBI compared with those of delivering CTR?

### Participants

Eligible participants are: (1) between 15 and 29 years old, (2) identify as a cisgender man or as transgender man or woman, (3) have had sexual contact with a man (oral or anal) in the last 6 months, (4) live in the DMA, (5) have unknown or negative HIV status, (6) and report binge drinking or using any illicit substance or nonmedical use of prescription drugs in the prior 3 months. The ATOD eligibility criteria are measured using the Alcohol, Smoking and Substance Involvement Screening Test (ASSIST) [49] to assess frequency of AOD use in the prior 3 months.

### Recruitment

Participants are recruited using Web-based advertisements on social media websites (eg, Facebook, Grindr), which will be tailored to target YMSMTG in the DMA. Recruitment will also occur in person at local venues and community outreach events in the region.

### Screening

Eligible participants will be invited for their baseline visit at the ASO closest to them: offices are available in Ann Arbor, Ypsilanti, Detroit, and Flint, allowing access by participants from across the DMA. Participants who present for participation in the trial will have already set up a study account online and completed an online baseline survey with informed consent given online. When they arrive for their first visit, they will be reconsented verbally and offered a physical copy of the consent form. A study counselor will be available to answer any questions that the participants may have about the study before they decide to participate. Participants who do not consent to participate in the trial will be offered free HIV testing and counseling. Resources will be readily available for providing tools to avoid ATOD-related risks (eg, reducing ATOD use or consequences), and referrals to community resources as needed (eg, psychosocial services, leisure activities not involving substance use).

### Randomization

Participants will be randomly assigned to 1 of the 4 conditions using a 1:1:1:1 treatment allocation. The treatment assignments will be generated with the use of a pseudo-random-number generator with permutated blocks that will be used to ensure balance between the numbers of YMSMTG assigned to each treatment. Assignments to the control or intervention arms will use concealment of allocation techniques designed to minimize assignment bias including generating, in advance, the sequence of assignment in sealed envelopes, which will be opened by the counselor at the time of randomization. When YMSM are randomized to receive CTR-only at a visit, they will receive standard CTR (30 min). YMSM randomized to SUBI at a study visit will receive the CTR that has been adapted to include the SUBI. On average, both conditions will last approximately 30 min.

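### As described, the whole two-visit arm is revealed to a counselor at baseline, so whoever delivers visit 1 can know the visit-2 condition; a two-part envelope would avoid this

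*Protocol article*

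**What the plan says.** Under Trial Design, the article gives the timing of randomization as "we randomize at baseline into a factorial RCT" and the structure of treatment as "The intervention comprises 2 visits separated by 3 months". The four arms are fixed sequences. Controls have CTR both times. The other CTR-first arm is defined as follows: "Experimental arm 1 (CTR+SUBI) will receive CTR at visit 1 and SUBI at visit 2". The remaining two arms both start with SUBI, and they part only at month 3, when one moves to CTR and the other repeats SUBI.

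Under Randomization: "Participants will be randomly assigned to 1 of the 4 conditions using a 1:1:1:1 treatment allocation". The mechanism for concealing allocation is to prepare in advance "the sequence of assignment in sealed envelopes, which will be opened by the counselor at the time of randomization".

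Under Intervention Fidelity and Supervision, the article acknowledges that counselors may vary in how they deliver sessions. It lists training with boosters, supervision, CTR delivery by site counselors who have not been trained in SUBI, and fidelity rating in both conditions. Session length is to be compared across arms and used as a covariate.

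No section mentions a separate visit-2 envelope or any step that keeps the visit-2 condition from staff until month 3.

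**The concern.** The trial randomizes to four sequences in order to learn how the order and number of SUBI sessions matter. That question relies on pairs of arms being the same through visit 1: the two CTR-first arms, and the two SUBI-first arms. If the person delivering visit 1 knows what comes at month 3, that sameness depends on the counselor's restraint.

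The behavior at risk is ordinary. A counselor who knows a participant will never receive SUBI might put more into the CTR session. One who knows SUBI is coming might leave a topic for later, or press harder for a return visit.

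Sessions are unblinded counseling. For seronegative participants, the success criterion in Statistical Analysis is two or more HIV tests, spaced by three months or more, inside 15 months. Encouragement to retest could plausibly move that outcome. Attendance at visit 2 also decides whether the second session is received at all. Nothing about delivering visit 1 requires knowledge of the visit-2 condition.

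**Working it through.** No figure in the article bears on this point, so the check is a reading of the sections together.

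**Step 1. What one assignment contains.** Trial Design places randomization at baseline, and Randomization makes it an allocation to one of four conditions. Each condition fixes both visits:

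| Arm | Visit 1 | Visit 2 (month 3) |
|---|---|---|
| Control | CTR | CTR |
| Experimental 1 | CTR | SUBI |
| Experimental 2 | SUBI | CTR |
| Experimental 3 | SUBI | SUBI |

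An envelope that shows the assigned condition therefore shows the visit-2 content as well.

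**Step 2. Who sees it, and when.** The counselor opens the envelope at randomization, which is at baseline. On the natural reading, a counselor knows the month-3 condition from visit 1 onward.

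**Step 3. Is the opener the person who delivers visit 1?** The article does not say. The Intervention section says interventionists are trained in CTR, so one person could open the envelope and deliver either condition. Intervention Fidelity and Supervision allows CTR to be given by other site counselors, so the opener could also be someone else. The supportable statement is that the visit-1 deliverer *can* know the visit-2 condition.

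**Step 4. Which comparisons are exposed.** Sample Size and Power and Statistical Analysis both define three primary tests, each active arm against CTR-CTR:

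- CTR-SUBI versus CTR-CTR: same visit-1 condition, meant to be identical until month 3. Exposed.
- SUBI-CTR versus CTR-CTR: visit 1 differs by design.
- SUBI-SUBI versus CTR-CTR: visit 1 differs by design.

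So one primary comparison in three has a visit-1 equality that foreknowledge can break. Outside the primary tests, SUBI-CTR versus SUBI-SUBI (one SUBI session against two) has the same exposure.

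**Step 5. Do the listed safeguards close the gap?** CTR counselors without SUBI training limit the leakage of SUBI technique into CTR. Supervision and fidelity rating may detect or deter drift, and a session-length covariate captures differences in time. None of these withholds the future assignment, and none is aimed at how strongly a counselor urges a participant to return or retest.

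**Step 6. How many participants a change could reach.** The Results section reports 142 randomized as of February 22, 2018 (36 + 36 + 34 + 36 = 142). Against the planned 600, that left 600 − 142 = 458.

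**The case against.** The strongest reply is that the key fact is inferred. The article does not say what is printed in the envelope, whether there is only one, or that its opener conducts visit 1. The Randomization section goes on to speak of being randomized to a condition at a given visit, which would be compatible with a visit-by-visit reveal. A journal article also commonly leaves envelope handling to the full protocol. In addition, the fidelity section already addresses uneven delivery, and a counselor not trained in SUBI has limited means to compensate with SUBI content.

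Much of this stands. A reader might infer that the visit-1 counselor certainly knows the visit-2 condition; the text supports only that this is possible. The safeguards deserve credit as a partial offset. But the point does not rest on silence alone. The article chose to describe the procedure, and as described it gives a counselor more than visit 1 needs.

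A reader might also infer that allocation concealment has failed. It has not been shown to. Sealed, pre-generated envelopes address foreknowledge before assignment, whereas this point concerns what is known afterward.

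Finally, a reader might infer that all three primary tests are compromised. The control arm is common to them, but in the other two the arms are meant to differ from visit 1 and the deliverer must know the visit-1 condition anyway.

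**Conclusion.** The point holds in conditional form, as a cheap improvement and not as a demonstrated bias. As described, the full arm is disclosed to a counselor at baseline. This opens an avoidable route to performance bias in CTR-SUBI versus CTR-CTR and in the SUBI-CTR versus SUBI-SUBI dosing contrast.

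The size cannot be estimated from the article. Nor can the direction: extra effort in the control arm would shrink the CTR-SUBI effect, while extra encouragement to return in the CTR-SUBI arm would inflate it. A reader might want to attach a loss of power or an inflated error rate to this, but any such figure would rest on an assumed shift for which the article gives no basis, so none is offered.

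The conclusion assumes that the envelope shows the whole arm and that the visit-1 deliverer sees it or is told. If the full protocol already stages the reveal, the point reduces to saying so in the article.

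**What to change.** For participants not yet randomized, keep the same pre-generated sequence and the same four arms, and put each assignment in a two-part envelope. The first part shows only the visit-1 condition and is opened at visit 1. The second shows the visit-2 condition and is opened at visit 2. Where visit-2 staffing has to be planned ahead, scheduling staff who do not deliver visit 1 hold that assignment. If a staged reveal is already in use, one sentence in the Randomization section is enough.

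The cost is re-packing the remaining envelopes, a short procedure note, and booking visit 2 without going through the visit-1 counselor. The sample size and planned analysis do not change.

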### Incentives

Participants will receive US $25 at each ASO visit and US $30 for each follow-up, making the total potential incentives (if all assessment visits are completed) US $200 per participant.

### Intervention

Study interventionists will be trained to deliver SUBI and will offer YMSMTG the opportunity to explore and strengthen motivations for changing their ATOD use during session. Interventionists are trained in CTR and typically have a Master’s degree in Public Health, Social Work, or a health-related discipline. The SUBI intervention consists of 2 components. Similar in style to other MI-based brief interventions for substance use and related risk behaviors [50-54], Component 1 focuses on employing MI to explore substance use (illicit drugs, misuse of prescription drugs, alcohol) and co-occurring sexual risk-taking with cultural and developmental tailoring for YMSMTG. There are 7 steps to Component 1 (see Table 1). To maintain the MI spirit, participants are asked for permission to begin the session and also when transitioning through different steps of each component.

**Table 1 table1:** Steps taken during Component 1 of the Swerve intervention compared with standard counseling, testing, and referral (CTR) steps.

Steps	Swerve intervention (SUBI^a^) Component 1: Alcohol, drugs, and sex	CTR: HIV prevention counseling
1	Rapport-building, exploring participants’ strengths and near-term goals	Introduce and orient the participant/client to the session and conduct of HIV test
2	Review of alcohol and substance use and conduct of HIV test	Identify risk behaviors and circumstances
3	Psychoeducation about alcohol/drugs and HIV risk	Identify safer goal behavior
4	Explore benefits to reducing substance use/harm reduction	Identify action steps
5	Build commitment to change	Provide referrals and support
6	Summary of Steps 1-6	Summarize and close
7	Explore possible reactions to HIV test results	—

^a^SUBI: substance use brief intervention.

In Step 1, counselors focus on MI-based engagement strategies to explore areas of strength and aspirations that the participant holds. Affirming these areas allows counselors to build rapport with participants and begin to uncover potential sources of motivation to change risky behaviors.

Step 2 invokes the MI process of focusing by reviewing participants’ recent substance use. Counselors explore participants’ frequency of current substance use, their motivations for use, and elicit any consequences to using substances. Possible links between substance use and risky sexual behaviors are examined by querying the potential role of substance use in having sex or hooking up and use of condoms. Counselors are trained to listen for, elaborate on, and evoke change talk as it begins to occur in Step 2 and throughout the remainder of the session. In Step 2, the counselor conducts the rapid HIV test.

In Step 3, counselors provide basic psychoeducation about how substance use and/or risky sex can impact risk for HIV infection, tailored to the participant’s own high-risk behaviors.

Step 4 seeks to elicit from participants any potential benefits to changing their substance use (eg, reducing use, ceasing use, or employing harm reduction), with a specific emphasis on how changing use can impact the risk for HIV transmission.

In Step 5, counselors reflect on participants’ perceived benefits and assess the importance of and readiness to change using the visual of a ruler in order to elicit their current stage of change. If participants are interested in changing, the counselor uses evocative questions to elicit a potential first step; for those not interested in making changes currently, the counselor elicits participants’ views on what might prompt them to consider a change in the future.

In Step 6, the counselor provides a strategic summary of what was discussed during Component 1. Here, counselors are beginning to transition into disclosing the HIV results from the test that was conducted in Step 2 and it is important for participants to think about what was discussed in each step as a whole.

Finally, in Step 7, counselors elicit and reflect how participants would react to a positive (reactive) or negative (nonreactive) result before disclosing the HIV results.

Component 2 varies based on the HIV test results (see Table 2), with the focus across intervention arms including either risk reduction counseling for HIV-negative participants or linkage and retention to HIV care among newly HIV-diagnosed individuals. Throughout Component 2, counselors remain grounded in the MI spirit and use MI skills to engage the participant in a collaborative conversation.

If participants’ results are nonreactive, repeat HIV testing and pre-exposure prophylaxis (PrEP) are the focal points of Steps 8 through 12. In Step 8, counselors elicit and reflect participants’ responses to receiving a nonreactive result.

Step 9 explores the benefits of repeat testing. Counselors discuss the window period, recommendation for testing every 3-6 months, and how participants feel about repeat testing, particularly eliciting concerns regarding the window period. As with change talk regarding substance use, counselors are trained to reflect selectively and affirm statements favoring repeat testing.

PrEP referrals are discussed in Step 10. Participants are asked what they know about PrEP, and counselors provide additional information and/or referrals to PrEP providers.

In Step 11, counselors tie the goals and strengths from Component 1 into encouraging repeat testing and PrEP evaluation. Possible barriers to repeat testing and PrEP evaluation are discussed along with strategies to overcome these barriers.

Step 12 summarizes what was talked about during Component 2 while affirming the strengths and goals from Component 1. Here, counselors elicit goals with regard to repeat testing and/or PrEP uptake and elicit steps to achieve these goals that are achievable, clear, and have a distinguishable end point. Barriers to achieving the goal are elicited and problem-solved, and strengths are affirmed as a means of supporting follow-through with the goals established. Counselors then thank the participants for their time and end the session. Alternatively, if participants’ HIV test results are preliminary reactive, linkage to HIV care is encouraged in Steps 8 through 11. Step 8 focuses on participants’ reactions to the test result. Counselors allow the participants to process their emotions and use empathic reflections in response and offering statements of hope.

**Table 2 table2:** Steps taken during Component 2 of the Swerve intervention.

Steps	Swerve intervention (SUBI^a^) Component 2a: Repeat HIV testing and PrEP^b^ (nonreactive results)	CTR^c^: HIV test counseling and partner services (nonreactive results)	Swerve intervention (SUBI) Component 2b: Linkage to HIV care (reactive results)	CTR: HIV test counseling and partner services (reactive results)
8	Response to testing nonreactive result	Meaning of test results	Response to testing HIV positive	Meaning of test results
9	Focus on repeat HIV testing	Cost and benefit analysis of testing	Focus on linkage to HIV care	Cost and benefit analysis of testing
10	PrEP referral	Interpretation of HIV test results	Links to Component 1 (goals, strengths, and substance use as a barrier)	Interpretation of HIV test results
11	Links to Component 1 (goals, strengths, and substance use as a barrier)	Reinforce plan for reducing risk based on test results	Summary and plan for action	Renegotiate risk reduction plan
12	Summary and plan for action	—	—	Discuss disclosure, partner services, appropriate referrals for medical evaluations, and early intervention services
13	—	—	—	Collect specimen for confirmatory testing^d^

^a^SUBI: substance use brief intervention.

^b^PrEP: pre-exposure prophylaxis.

^c^CTR: counseling, testing, and referral.

^d^Each ASO has specific procedure for confirmatory testing. Detroit-Blood draw for confirmatory testing: results in 3 days. Ypsilanti-Rapid test for confirmatory testing: results in 1 min. Flint-Rapid test for confirmatory testing: results in 20 min.

With permission, counselors begin to discuss the importance of linkage to HIV care in Step 9. Counselors explain how people with HIV can live healthy lives provided that they attend medical appointments and take medications while also exploring the participant’s perceived benefits of seeing a HIV medical provider.

Step 10 links the strengths and goals from Component 1 as a tool to continue to encourage linkage to care. Possible barriers to linkage to care are explored, with an emphasis on the potential impact of substance use.

Step 11 reflects on the participants’ goals for next steps toward linkage to care with an emphasis on eliciting goal-setting with goals that are achievable, clear, and have a defined end point. Counselors provide support to participants by affirming their strengths to meet these goals. Counselors thank the participants for their time and end the session.

#### Substance Use Brief Intervention at Study Visit 2

For those who received a nonreactive HIV test result at visit 1 and who are randomized to receive SUBI at study visit 2, the same intervention components and steps are delivered, as described above. For those who received a reactive test result at visit 1, the SUBI session focuses employing MI skills to address adherence with HIV care and the role of substance use.

